### Determining cost-effectiveness

If a significant impact of DS CBT on both effects and costs is demonstrated, ICER will be estimated in terms of costs per QALY gained. ICER will be estimated for the total cost (health sector costs plus patient costs plus societal productivity costs) and for the health sector costs only (statutory health insurance perspective). The non-parametric bootstrap method will be employed to generate confidence intervals around the ICER estimates derived from the study sample [38,39]. Uncertainty surrounding the ICER will also be presented on the cost-effectiveness plane [40,41] and as the cost-effectiveness acceptability curve [42,43].

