**Methods/Design:**

Within-trial economic evaluation of the diabetes-specific cognitive behaviour therapy for subthreshold depression. Patients with diabetes and subthreshold depression are randomly assigned to either 2 weeks of diabetes-specific cognitive behaviour group therapy (n = 104) or to standard diabetes education programme only (n = 104). Patients are followed for 12 months. During this period data on total health sector costs, patient costs and societal productivity costs are collected in addition to clinical data. Health related quality of life (the SF-36 and the EQ-5D) is measured at baseline, immediately after the intervention, at 6 and at 12 months after the intervention. Quality adjusted life years (QALYs), and cumulative costs will be estimated for each arm of the trial. Cost-effectiveness of the diabetes-specific cognitive behaviour group therapy will be analysed from the perspective of the German statutory health insurance and from the societal perspective. To this end, incremental cost-effectiveness ratio (ICER) in terms of cost per QALY gained will be calculated.

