## Background

Depression is a highly prevalent disorder with a substantial impact on quality of life and societal cost [1,2]. This applies in particular to patients with diabetes, since depression has been shown to be more prevalent among these patients as compared to those without diabetes [3-5]. Previous research demonstrates that comorbid depression in patients with diabetes is associated with poor self care, i.e. adherence to medication, diet, exercise and smoking cessation [6-8], additive functional impairment and work disability [9], poorer glycaemic control [10], higher risk of microvascular and macrovascular complications [11,12], decreased quality of life [13], and higher mortality [14,15] as compared to patients with diabetes only. Many studies also found higher overall health care cost in depressed patients, not explained by higher mental health treatment costs alone. This association persisted even after adjustment for comorbid medical conditions [see e.g. [7,16-19]]. A US study [17] found 4.5-times higher total annual healthcare costs for Medicare patients with diabetes and comorbid depression than for diabetic patients without depression ($247,000,000 and $55,000,000, respectively; *P *< 0.0001 (cost adjusted to reflect August 2001 dollars).

Hence, the more effective depression treatment might not only improve health outcomes, but also reduce total health service utilization and therefore costs. Put differently, additional costs for improved depression treatment could be offset by reduction in other healthcare costs. In the IMPACT trial [20] for example, systematic depression treatment in older adults with diabetes had significant clinical benefit with no increase in overall healthcare costs. The Pathways Study [21] also found that over a 2-year period the increased costs associated with enhanced mental health treatment were offset by savings in total medical expenditures.

Cost-effectiveness of treatment options for depression has been mainly evaluated for major depression co-occurring with diabetes. However, there is a need to examine the cost-effectiveness of therapies for subthreshold depression as well, since there is evidence that about 20% of patients with diabetes have elevated depressive symptoms without meeting criteria for major clinical depression [4,5]. In what follows, a within-trial economic evaluation of a diabetes-specific cognitive behaviour therapy in patients with type 2 diabetes and subthreshold depression is outlined.

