### Within-trial economic evaluation

The objective of the economic evaluation, which is conducted alongside the trial, is to estimate the cost-effectiveness of the DS-CBT in terms of costs per quality adjusted year (QALY) from the perspective of the German statutory health insurance and from the societal perspective. To this end an incremental cost-effectiveness ratio (ICER) will be calculated, i.e. the ratio of the difference in costs between DS-CBT and DEP groups divided by the difference in QALYs gained in each group. Under statutory health insurance perspective on cost, ICER will be calculated using health sector costs only. Adopting the societal perspective, also patient costs and societal productivity costs will be added to the calculation of the ICER.

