### Sensitivity analyses

Besides statistical uncertainty (sampling variation) with regard to costs and effects, every economic evaluation may contain some degree of data imprecision (e.g. resource costs/prices) and methodological controversy (e.g. derivation of utility weights, discount rate), which should be accounted for. To handle this type of uncertainty, sensitivity analysis is usually employed [25,44]. In the sensitivity analysis (uncertain) parameter(s) of the base-case analysis are varied to determine if changes in these parameters influence the results. Univariate sensitivity analyses will be performed by varying health service unit costs and utility weights (see Table 2). To appreciate the potential influence of missing responses and of the imputation method chosen, complete case analysis will be performed. We will report both the revised point estimates and revised confidence intervals for costs, effectiveness, and cost-effectiveness that result from the sensitivity analyses.

**Table 2 T2:** Summary of planed sensitivity analyses

Parameter/methodological assumption	Base-case	Sensitivity analysis
Utility weights for QALYs	derived from the EQ-5D	derived from the SF-36

Unit costs/prices of resource use	data from published sources and official statistics for Germany	varied within a plausible range

Missing data	multiple imputation	complete case analysis

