## Discussion

In the context of the trial, it might be argued that, if true randomisation is achieved, any differences in cost between treatment arms can be attributed to the study intervention [45]. Hence, data on utilisation of a broad range of health services will be collected in the trial. This approach allows measuring any changes in resource use related to the interventions being compared. On the other hand, however, it may complicate the detection of statistically significant difference in health service costs, since the latter have been shown to be highly variable and therefore to require larger overall sample sizes [45,46].

Information on healthcare utilisation other than DS-CBT and DEP sessions will be collected by self-report by means of the cost questionnaire. To our knowledge no standard and validated instruments for collecting resource use data in clinical trials are available in Germany. Hence, we developed a data collection instrument specifically for this trial. The questionnaire was pilot tested, but has not yet been validated against other data sources. Recall bias may potentially occur, since resource use will be measured over the previous 6 months. However, there is no conclusive evidence regarding whether a prospective (a cost diary) or a retrospective (a questionnaire) instrument should be better applied and regarding an appropriate recall interval [45]. Van den Brink et al. found that for the assessment of healthcare utilization in economic evaluations alongside clinical trials, a cost questionnaire may replace a cost diary for recall periods up to 6 months [47] and that such patients' self-reports are a valid source of data on days of hospitalization and out-patient visits, whereas costs of medication may be underestimated [48].

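### The ICER is made conditional on significant differences in both QALYs and costs, which contradicts the stated objective and can withhold the joint cost-effectiveness analysis

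*Protocol article*

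**What the plan says.** The protocol article speaks to whether an ICER will be produced in four places.

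- Abstract, Methods/Design, no condition: "incremental cost-effectiveness ratio (ICER) in terms of cost per QALY gained will be calculated".
- Within-trial economic evaluation. The objective "is to estimate the cost-effectiveness of the DS-CBT in terms of costs per quality adjusted year (QALY"), from the statutory health insurance and the societal perspective, followed by: "To this end an incremental cost-effectiveness ratio (ICER) will be calculated". No condition.
- Determining cost-effectiveness, conditional: "If a significant impact of DS CBT on both effects and costs is demonstrated, ICER will be estimated". The next sentences name the two cost perspectives, the bootstrap interval for the ICER, the plane and the acceptability curve. The last two are described as showing the uncertainty around the ICER.
- Sensitivity analyses, no condition: "We will report both the revised point estimates and revised confidence intervals for costs, effectiveness, and cost-effectiveness".

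The section on statistical analysis of costs and effects provides, without condition, the cost differences with bootstrap 95% confidence intervals and a regression analysis of QALYs.

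**The concern.** The document gives two incompatible instructions. Under one, the ICER is the planned output. Under the other, it exists only if two separate tests are both significant. Revised cost-effectiveness estimates in a sensitivity analysis presuppose a base-case estimate that the conditional rule may have withheld.

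The conditional rule is also the wrong one to keep. Whether an intervention is cost-effective is a question about the cost and QALY differences together. The joint evidence can be informative when one or both differences are non-significant, and the bootstrap, the plane and the acceptability curve exist to show it. Non-significance is a reason to show wide uncertainty, not to leave the estimate out.

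The rule bites in the situation that the Background puts forward as attractive: "additional costs for improved depression treatment could be offset by reduction in other healthcare costs". A better outcome at about equal cost fails the cost test. The Discussion adds, of collecting a broad range of service use, that "it may complicate the detection of statistically significant difference in health service costs", and that such costs need larger samples. At stake are the ratio and its joint uncertainty, which are the stated purpose of the economic evaluation.

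**Working it through.** **1. What the trial is sized for.** Inputs from the sample size section: remission 65% versus 40%, two-sided α = 0.05, power 90%, loss 20%. With the arcsine formula, h = 2·asin(√0.65) − 2·asin(√0.40) = 0.506, and n = 2(1.960 + 1.282)²/h² = 82.06, rounded up to 83 per arm. Then 83/0.80 = 103.75, so 104. The stated 83 and 104 reproduce. The calculation covers remission only; no power is stated for QALYs or costs.

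**2. What significance requires.** The level for the condition is not stated; I take two-sided 5%, in line with the 95% intervals. The standard error of a difference in SD units is √(2/n).

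- At 83 per arm it is 0.155. A difference must exceed 1.96 × 0.155 = 0.30 SD to be significant, and 80% power needs (1.960 + 0.842) × 0.155 = 0.43 SD, for costs and QALYs separately.
- At 104 per arm the corresponding figures are 0.27 and 0.39 SD.

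**3. A bound that needs no assumed SD.** P(both significant) ≤ P(cost significant). If the true cost difference is zero, the right-hand side is 5%. So at most about 5% of trials pass, whatever the QALY gain, the sample size or the correlation. This supposes one cost measure is tested; the protocol does not say whether the condition refers to total or health sector costs.

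**4. Chance of passing otherwise.** The protocol gives no SDs or expected differences, so these are assumptions in SD units (normal approximation, cost and QALY differences independent). Power for a true difference d is Φ(d/SE − 1.96) + Φ(−d/SE − 1.96). For example, at 83 per arm d = 0.3 gives 0.489 and d = 0.2 gives 0.252, product 0.123.

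| QALY difference (SD) | Cost difference (SD) | Both significant, 83/arm | Both significant, 104/arm |
|---|---|---|---|
| 0.3 | 0 | 2.4% | 2.9% |
| 0.3 | 0.1 | 4.8% | 6.5% |
| 0.3 | 0.2 | 12% | 18% |
| 0.3 | 0.3 | 24% | 34% |
| 0.5 | 0.2 | 23% | 29% |
| 0.5 | 0.3 | 44% | 55% |
| 0.5 | 0.5 | 80% | 90% |

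An illustration in natural units, all values assumed: 104 per arm, QALY SD 0.18, gain 0.04, cost SD EUR 6000, cost difference EUR 500, correlation −0.2. The standard errors are 0.18 × √(2/104) = 0.025 and 6000 × √(2/104) = EUR 832. QALYs are significant in 36%, costs in 9%, both in about 2.3%. Varying the gain over 0.02–0.08, the cost difference over EUR 0–1000 and the cost SD over EUR 3000–6000 gives 0.7% to 59%.

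**5. What happens to an ICER that passes.** In that illustration, among trials that pass, the mean cost difference is about EUR 1470 (true 500) and the mean QALY gain 0.064 (true 0.04). Each increment is inflated because its power is low. The ratio behaves differently (simulated medians among trials that pass, same QALY SD and correlation):

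| Gain | Cost difference | Cost SD | True ICER | Median ICER given passing |
|---|---|---|---|---|
| 0.04 | EUR 500 | 6000 | 12,500 | about 30,000 |
| 0.08 | EUR 1000 | 3000 | 12,500 | about 14,500 |
| 0.04 | EUR 1000 | 3000 | 25,000 | about 18,000 |
| 0.02 | EUR 1000 | 3000 | 50,000 | about 18,500 |

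The same holds in SD units at 83 per arm with zero correlation: QALY 0.3 / cost 0.1 gives 2.7 times the true ratio, 0.3/0.2 gives 1.4 times, 0.5/0.5 gives 1.0 and 0.2/0.5 gives 0.53 times. The direction depends on which difference has the lower power.

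**The case against.** Four things can be said for the plan.

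- **Both increments are reported anyway.** This stands. A reader can divide the QALY difference into the cost difference, so the loss is narrower than the whole evaluation. The reader cannot, however, recover the joint distribution, and so cannot rebuild the plane, the acceptability curve or a valid interval for the ratio.
- **The condition may govern only its own sentence.** The sentences on perspectives, bootstrap, plane and curve carry no condition of their own. This stands as a possible reading. But they describe uncertainty around an ICER that the first sentence has just made conditional, so the natural reading is that they fall with it. That the text allows both readings is itself a reason to repair it.
- **A reader might infer that the trial will usually end without an ICER.** The documents do not support that. The Background says costs could be offset and the Discussion that detection may be complicated; neither predicts a zero difference. With differences of about 0.5 SD on both axes the condition would be met about 80% of the time at 83 per arm.
- **A reader might infer that any ICER reported under the rule is exaggerated.** That is false in general. The two increments are each inflated when their power is low, but their ratio can come out too high, too low or about right.

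The rule also affects reporting only: no data are lost, and the clinical primary endpoint is untouched.

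**Conclusion.** The point holds. The double-significance condition contradicts the abstract, the objective and the sensitivity analyses, and it is unsound because it tests separately what has to be judged jointly. Followed as written, it can withhold the ICER and, on the natural reading, its interval, the plane and the acceptability curve. That may well happen.

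The firm figure is a ceiling of about 5% if costs are fully offset, assuming a two-sided 5% test of one cost measure. Beyond that the chance of passing cannot be fixed from the document: under assumed SDs and differences it ranges from below 1% to about 80%, and to 90% if all 104 per arm were evaluable. These figures use normal approximations for skewed costs. An ICER that passes is selected, with bias whose direction cannot be predicted. Because the rule can suppress the study's own stated output, it should be corrected before analysis.

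**What to change.** Delete the significance condition in the section on determining cost-effectiveness. State instead that, whatever the p-values, the following are reported for the statutory health insurance and the societal perspective:

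- incremental costs and incremental QALYs;
- the ICER, or a statement of dominance when the point estimate lies in the south-east or north-west quadrant;
- the joint bootstrap distribution on the cost-effectiveness plane;
- the acceptability curve.

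This brings the section into line with the abstract, the objective and the sensitivity analyses. The cost is one sentence. No further data are needed, and the design, sample size and clinical analysis do not change.

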### Imputation of missing information on costs and effects

Data will be analysed according to the intention to treat principle. A multiple imputation approach based on propensity scoring will be used to account for missing information with regard to effects and costs. Baseline variables (e.g. age, gender, cost at baseline, etc.) will be entered into a logistic regression to predict the chance of a missing value [33,34]. Available data will be arranged into quintiles based on this predicted probability (propensity score) and a replacement value for missing data will be selected at random from the available data points within the same quintile. By choosing a value at random within the same quintile the principle of multiple imputations could be employed, whereby each missing value is replaced by m > 1 simulated values [35-37]. Each of *m *resulting data sets will be analysed as described above and combined to produce a single result that takes uncertainty in the imputation process into account.

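### The ICER and its bootstrap interval depend on significance of both effects and costs in one section but not elsewhere, so the plan yields either probably no cost-effectiveness interval or one that may mix quadrants; net monetary benefit avoids both

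*Protocol article*

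**What the plan says.** All places are in the protocol article.

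- **Determining cost-effectiveness** opens with a condition: "If a significant impact of DS CBT on both effects and costs is demonstrated, ICER will be estimated in terms of costs per QALY gained". Two ICERs follow, one on total cost and one on health sector costs. The text does not say which cost difference has to be significant.
- The same section sets the interval method: "The non-parametric bootstrap method will be employed to generate confidence intervals around the ICER estimates derived from the study sample". It adds graphical displays: "Uncertainty surrounding the ICER will also be presented on the cost-effectiveness plane", and an acceptability curve.
- **Within-trial economic evaluation**, which states the objective, has no condition: "To this end an incremental cost-effectiveness ratio (ICER) will be calculated". Nor has the abstract: "incremental cost-effectiveness ratio (ICER) in terms of cost per QALY gained will be calculated".
- **Sensitivity analyses** promises "revised confidence intervals for costs, effectiveness, and cost-effectiveness that result from the sensitivity analyses", without repeating the condition.
- **Imputation of missing information on costs and effects** has each imputed data set analysed and the results "combined to produce a single result that takes uncertainty in the imputation process into account".
- **Discussion** says of the broad collection of resource use that "it may complicate the detection of statistically significant difference in health service costs".

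Incremental net benefit is not mentioned.

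**The concern.** The stated objective is cost per QALY from two perspectives. The article leaves open whether that result will be reported when either difference is not significant, and each reading has a problem.

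**If the condition is applied,** the result depends on two significance tests in a trial sized only for remission. The Discussion accepts that a significant cost difference may be hard to detect, and the Background leaves the sign of that difference open because savings may offset the added cost. The likely outcome is no ICER and no interval. Yet the uncertainty of a non-significant pair of differences is what a decision-maker needs to see.

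**If the condition is not applied,** the interval is for a ratio whose numerator and denominator can both change sign. A negative ratio can mean better and cheaper (south-east quadrant of the plane) or worse and dearer (north-west). A positive ratio can mean a gain bought at a cost (north-east) or a loss with a saving (south-west). Ordering such ratios and cutting at percentiles gives limits with no coherent meaning, and the ratio is unstable when the QALY difference is near zero.

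A mixed case is also possible: the condition may be met for one cost perspective only, or met in the base case and lost in a sensitivity analysis.

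**Working it through.** **1. The plan's own figure.** The only sample size given is for remission: 65% against 40%, two-sided 5%, 90% power, 83 per arm. The pooled two-proportion formula gives 82 per arm, and power at 83 is 90.4%. Then 83/(1 - 0.20) = 104. This reproduces the plan. No figure is given for costs, QALYs or the ICER.

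**2. Condition applied and just met.** Take z = 1.96 for both differences, uncorrelated. The share of replicates in the observed quadrant is 0.975 x 0.975 = 0.951. The share with a QALY difference of opposite sign is 2.5%. At z = 2.5 on both, about 1.2% leave the quadrant and 0.6% have the opposite sign in the denominator. Under the condition, the base-case ratio interval is reasonably well behaved.

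**3. How likely the condition is to be met.** Assumed inputs: QALY SD 0.18, gain 0.03; cost SD EUR 5,000, difference EUR 300; 104 per arm; correlation of the two differences -0.2; normal approximation.

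- SE(QALY) = 0.18 x sqrt(2/104) = 0.0250, so z = 0.03/0.0250 = 1.20
- SE(cost) = 5,000 x sqrt(2/104) = EUR 693, so z = 300/693 = 0.43
- Chance of significance: 22% for QALYs and 7% for costs. Jointly this is 0.225 x 0.072 = 1.6% ignoring correlation, and about 1.1% with correlation -0.2.

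Wider assumed ranges at 83 per arm, uncorrelated (QALY SD 0.15 to 0.25, gain 0.01 to 0.05; cost SD 5,000 with difference -500, 0 or +300, or cost SD 10,000 with +300), give about 0.3% to 6%. The joint chance can never exceed the smaller single chance. With the first set of inputs it therefore stays at or below 22% however large the cost difference.

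**4. Condition not applied.** With the inputs of step 3, the replicates divide as follows.

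| Quadrant | Meaning | Share |
|---|---|---|
| North-east | better, dearer | 58% |
| South-east | dominant | 31% |
| North-west | dominated | 9% |
| South-west | worse, cheaper | 2.5% |

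Negative ratios: 31% + 9% = about 40%. Of these, 77% are dominant and 23% dominated. With a true cost difference of 0, 53% are negative. The percentile interval runs from about EUR -191,000 to +218,000 per QALY around a point estimate of 300/0.03 = EUR 10,000. Over the wider ranges the largest quadrant holds only about 30% to 73% of replicates.

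**5. Condition met in the base case, lost in a variant.** If z = 1.96 on both axes with 104 per arm, a complete-case analysis of 83 per arm with the same estimates and SDs has z = 1.96 x sqrt(83/104) = 1.75. Both differences are then non-significant, and about 92% of replicates lie in one quadrant. The SF-36 utilities can shift the QALY difference as well.

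**6. The alternative on the same draws.** INMB = lambda x QALY difference - cost difference. Its variance is lambda² x SE(QALY)² + SE(cost)² - 2 x lambda x correlation x SE(QALY) x SE(cost). At an assumed lambda of EUR 20,000 the estimate is 600 - 300 = EUR 300. The SE is sqrt(499² + 693² + 0.4 x 499 x 693) = about EUR 932, and the 95% interval is about EUR -1,530 to +2,130. It has one meaning in every quadrant.

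**The case against.** The strongest reply is that the bootstrap interval belongs to ICERs estimated under the opening condition. A reader might infer that the planned headline interval will be uninterpretable in the likely case of a small QALY gain and a cost difference near zero. Read alone, the section Determining cost-effectiveness does not support that: in that case it produces no ICER, and when the condition is met the replicates lie mostly in one quadrant (step 2). This part of the reply stands. The split in step 4 describes only a reading without the condition.

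Second, the plane and acceptability curve are already planned. The plane shows any spread over quadrants, and the curve gives, at each willingness to pay, the probability that net benefit exceeds zero. It would be wrong to say that the plan relies on the ICER interval alone. However, both displays are described as showing uncertainty around the ICER, so the condition may suppress them too. The curve also gives probabilities, not an estimate with an interval.

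Third, a reader might infer that the imputation section requires ICERs to be averaged over imputed data sets. It does not. It refers back to the analyses of cost differences and QALYs, and pooling those before forming a ratio fits the text.

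Fourth, the article does not say how bootstrap ratios are ordered, and the method papers it cites are not available here. The objection to the interval is therefore limited to percentile-type methods.

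Fifth, a revised interval presupposes a base-case interval, and the loss in step 5 is modest. That is fair for complete cases. It does not settle what is reported when significance is lost, or is present for one perspective only.

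**Conclusion.** The point holds as an inconsistency with a practical consequence. The section that fixes the analysis makes the ICER conditional on two significant differences, while the objective and the abstract do not. The section on sensitivity analyses is silent, and the cost difference to be tested is not named.

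Enforced, the condition probably leaves the stated objective without a cost-effectiveness interval: about a 1% chance of meeting it under the main assumptions, and 0.3% to 6% over the wider ranges. Not enforced, a percentile-type ICER interval can combine replicates of opposite meaning, with about 40% negative ratios in the illustration.

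The SDs, differences, correlation and willingness-to-pay value are assumptions, because the documents give none. Larger true differences would raise the chance of meeting the condition and reduce the mixing. The contradiction between sections does not depend on any of them. This should be changed; it does not affect the clinical primary endpoint.

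**What to change.** - Drop the significance condition, so that Determining cost-effectiveness agrees with the abstract and Within-trial economic evaluation.
- For both perspectives, in the base case and in each sensitivity analysis, report incremental net monetary benefit with a 95% CI over a stated range of willingness to pay, whatever the significance of either difference.
- In imputed analyses, estimate it in each imputed data set and pool by Rubin's rules. It is linear in the two differences, so this is straightforward. Complete-case analyses need no pooling.
- Always show the already planned cost-effectiveness plane and acceptability curve.
- Report the ICER as a point estimate, with an interval only if essentially all replicates have a QALY difference of the same sign.

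The cost is wording, somewhat more reporting, and the need to state a willingness-to-pay range in advance. The data and the bootstrap output stay the same.
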